#### **Methods**

This is a single-blind, two-arm cluster randomised controlled trial involving 28 psychiatric hospital wards across Finland. Units will be randomised to receive either a staff educational programme delivered by the team of researchers, or standard care. The primary outcome is the incidence of use of patient seclusion rooms, assessed from the local/national health registers. Secondary outcomes include use of other coercive methods (limb restraint, forced injection, and physical restraint), service use, treatment satisfaction, general functioning among patients, and team climate and employee turn-over (nursing staff).

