### *Setting and sample*

This is a nation-wide study to be conducted across Finland in hospitals with psychiatric beds. Finnish mental health services are arranged by municipalities (N=317 [68]), each individual municipality forms joint municipal authorities with other municipalities, or hospital districts, and are supplemented by private and third sector services (e.g.

## SUPPLEMENT 1

associations and foundations). People in need of inpatient psychiatric care are treated in general health services (e.g. health centres) or specialised medical care services organised by hospital districts [69]. This study will be conducted in hospitals with psychiatric beds in the non-private sector. Hospitals as cluster will be recruited and randomised.

Inclusion criteria of required participating hospital organisations are: Finnish-speaking, to have at least 1 psychiatric ward, open 24 hours a day, seven days a week, and, when necessary, are able to use coercive measures defined in the Finnish Mental Health Act (1116/1990, [70]) (seclusion room, limb restraint, forced medication, physical restraint). Wards will be excluded if they are specialised in forensic, psychogeriatric, or child and adolescent mental health care alone or if a similar type of project is underway or is planned to start there. In total there are 28 eligible hospitals. Once a hospital is allocated to any comparison arm, all health care professionals working in wards of the hospital and patients admitted to those wards are eligible to participate to the study. Based on the Finnish health statistics of the National Institute for Health and Welfare [17], patients with a primary diagnosis of schizophrenia represents the second most common diagnostic group in psychiatric hospitals, after people with depression or recurrent depressive disorder [17]. People with schizophrenia are treated in psychiatric hospitals if they are in an acute phase and need for specialized care: 60% of all hospitalised patients in 2014 were hospitalised through an emergency admission [17].

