### Study procedure

#### *Recruitment and randomisation*

Written information letter describing the study are to be sent to the administrators of each hospital organisation. They are given up to four week-time to show their preliminary interest and willingness to participate. This allows an adequate time for them to think through their decision and ask any questions related to the study.

Hospital organisations, within which there will be eligible wards, agreeing to participate will be randomly allocated to either receive staff education intervention (intervention group) or not receive staff education (passive control group). This allocation is organised by the research group as soon as baseline information of the wards is collected. The unit of randomisation is the hospital organisation within which there will be psychiatric wards. The cluster design will be used to avoid contamination in intervention effects between individual staff members. We will use centralised randomisation at the University of Turku (Department of Mathematics and Statistics) stratified by number of patient beds and nursing staff to assure as similar number of participants as possible in the intervention group as in the passive control group. Randomisation will be fully concealed and computer-generated by an independent statistician, who is not involved in the study. Investigators enrolling wards will not be able to foresee the assignment.

Data analysts will be kept blinded to allocation. Due to the type of intervention, allocation will be unmasked after randomisation to patients and their relatives, contact persons on each ward, health care staff delivering patient care on the wards, and the researchers participating in the intervention design and implementation; this will reflect real-world care. The Data Management Committee (DMC) will undertake ongoing safety surveillance. Investigators running the preliminary analysis for the DMC will be masked to data until investigators release the database. In addition, the statisticians and the National Register holder [71] responsible for Finnish routine data used in this study will be masked to ward allocation and patient data in each arm.

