### **Power and sample size**

We have systematically searched for, but found no directly relevant past work [31, 91]. We assume that if the data will be obtained from local hospital registers by sampling 7 clusters (hospitals) with 265 subjects each in intervention group and 7 clusters with 265 subjects each in control group, we will have 80% power to detect a difference between the

## SUPPLEMENT 1

group proportions of -0.0400. The control group proportion is 0.1100. The intervention group proportion is assumed to be 0.1100 under the null hypothesis and 0.0700 under the alternative hypothesis. The test statistic used is the two-sided Z test (unpooled) with an overall significance level at 0.05. We may assume based on the hospital registers that sample size for the total population admitted in the study wards in one year will be 3710. However, if we consider a loss of 20% patients in the local care registers, [92] the total number of patients on the randomised wards should be about 4454 patients. (PASS 11 software [93]). Further, if we assume 50% response rate for patient survey [94] out of possible 3710 participants, we will assume that we will obtain 928 filled questionnaires during 6 month survey data collection period. The sample size calculation was adjusted for intra-cluster correlation at 0.005.

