### **Data analysis**

#### *Statistical analysis*

The Data Management Committee including a statistician outside of the research team will verify the statistical analysis and the Quality Assurance Process.

The baseline characteristics of the units, and respondents (patients, staff members) will be summarised using descriptive analysis (mean [standard deviation], median [interquartile ranges] or proportions) and compared between each intervention group, respectively.

The analysis will be carried out on an intent-to-treat (ITT) basis. Assumptions of normality of the residuals will be investigated. For the primary outcome, incidence of coercion methods used at the baseline (year 2015), year 2016 (at the beginning of 2017), and year 2017 (at the beginning of year 2018) will be calculated. Possible differences in patient characteristics between the intervention and the control group at baseline will be tested by Chi-Square or t-tests based on type of variables. This analysis will help to decide whether baseline characteristics of patients should be adjusted for in the model for the primary outcome comparison after intervention. The hierarchical (participant nested within ward) Poisson model will be used to estimate and test the relative risk of being coerced in the intervention and the control group, which takes into account the length of staying of patient's in hospitals. With the same principle, for secondary outcomes, a hierarchical linear model will be used for normally distributed variables such as patient satisfaction and team climate, a hierarchical logistic model for dichotomous outcomes such as any admission or any adverse event, and the Poisson model for hospitalisation stay lengths or time spent in a seclusion room. A sensitivity analysis will be conducted by comparing the primary data at the follow-up and the fidelity information [47]. If poor fidelity was found for the primary data, we may consider evaluating change rate of coercive methods use between the two groups using all three measures over time by applying repeatedly measured models with random effects of hospital clusters. The results from the secondary analyses will be treated as exploratory. Estimates and confidence intervals will be reported only. The CONSORT guidelines for randomised trials [95] will be followed throughout our data analysis and the reporting of our study results. This study protocol follows the recommendations of the SPIRIT Statement [96].

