### Study status

To date, we have recruited 15 hospitals, in which a total of 28 psychiatric wards are willing to participate. Wards were randomised in May 2016 (13 intervention wards, 15 in comparison wards).

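### The primary model clusters patients by ward only, while the protocol names the hospital as the randomised and powered unit in some places and the ward in others; if hospitals were randomised, the primary test is anti-conservative.

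*Protocol*

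**What the plan says.** On the unit randomised, the protocol gives two accounts.

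- **Hospital.** Setting and sample: "Hospitals as cluster will be recruited and randomised". Recruitment and randomisation: "The unit of randomisation is the hospital organisation within which there will be psychiatric wards". Power and sample size rests on "sampling 7 clusters (hospitals) with 265 subjects each in intervention group and 7 clusters with 265 subjects each in control group", with an intra-cluster correlation (ICC) of 0.005.
- **Ward or unit.** The Abstract describes a trial "involving 28 psychiatric hospital wards across Finland. Units will be randomised to receive" one of the two conditions. Study status reports: "Wards were randomised in May 2016 (13 intervention wards, 15 in comparison wards").

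Study status also says "we have recruited 15 hospitals, in which a total of 28 psychiatric wards are willing to participate", so at least some hospitals contribute more than one ward.

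On the analysis, the Statistical analysis section gives the primary model: "The hierarchical (participant nested within ward) Poisson model will be used to estimate and test the relative risk of being coerced". The secondary models are to be built on the same principle. Hospitals enter as a random effect only in an optional repeated-measures analysis, to be considered if fidelity turns out poor: "applying repeatedly measured models with random effects of hospital clusters".

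**The concern.** In a cluster trial the analysis has to respect the unit that was allocated. If whole hospitals were allocated, the trial has 15 independent units. A model with a ward effect and no hospital effect treats 28 wards as independent. Wards of one hospital share an arm and plausibly share management and seclusion practice. Any positive correlation between them is then left out of the standard error of the primary relative risk, so its confidence interval is too narrow and its p-value too small.

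This is not a detail left open for a statistical analysis plan. The protocol states the nesting explicitly, and the nesting does not match the unit that the protocol names as randomised and uses for power. The comparison affected is the trial's one primary test.

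**Working it through.** **Inputs from the protocol.** 15 hospitals and 28 wards, split 13 and 15 (Study status). From Power and sample size: 7 + 7 hospitals of 265 patients, 3710 in total, proportions 0.11 and 0.07, ICC 0.005, two-sided 5% level.

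**Inputs assumed.** The protocol gives neither the share of the ICC that lies between hospitals nor the number of wards per hospital. Both are varied below.

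**1. The protocol's own figure.**
- Design effect: 1 + (265 − 1) × 0.005 = 2.32.
- Effective size per arm: 7 × 265 / 2.32 = 1855 / 2.32 = 799.6.
- Standard error: √[(0.11 × 0.89 + 0.07 × 0.93) / 799.6] = 0.01428.
- Power: Φ(0.04 / 0.01428 − 1.96) = Φ(0.84) = 80.0%.

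The stated 80% reproduces with hospitals as clusters. This calculation correlates all patients of a hospital at 0.005, whichever ward they are on. The planning model therefore puts the whole ICC at hospital level.

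**2. Approximate type I error of a ward-only test when hospitals are randomised.**
- Wards per hospital: 28 / 15 = 1.87. Patients per ward: 3710 / 28 = 132.5.
- Let s be the share of the ICC at hospital level. Two ward means in one hospital correlate at r = 0.005s / (0.005 + 0.995 / 132.5) = 0.005s / 0.01251 = 0.40s.
- The variance of the treatment contrast is understated by the factor 1 + (1.87 − 1) × r.
- Type I error = 2 × [1 − Φ(1.96 / √factor)].

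| Share s | r | Factor | Type I error |
|---|---|---|---|
| 0 | 0 | 1.000 | 5.0% |
| 0.5 | 0.20 | 1.173 | 7.0% |
| 1 | 0.40 | 1.346 | 9.1% |

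This approximation treats hospitals as equal in size and the ward variance as known. An uneven spread makes matters worse. Take 4, 3, 2, 1, 1, 1, 1 wards in one arm and 5, 3, 2, 1, 1, 1, 1, 1 in the other. The factor in each arm is 1 + (Σm²/Σm − 1) × r, where m is the number of wards in a hospital:
- At r = 0.40 it is 1 + (33/13 − 1) × 0.40 = 1.615 in one arm and 1 + (43/15 − 1) × 0.40 = 1.747 in the other.
- Weighting these by 1/13 and 1/15 gives about 1.68, and a type I error of about 13%.

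**3. Simulation at ICC 0.005.** Ward means were drawn from normal distributions, with 40,000 runs per row. The ward-level test was judged against t with 26 df or against 1.96. The near-equal layout has two wards in every hospital except one per arm. The uneven layout is the one above.

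| Share s | Layout | Ward test, t | Ward test, 1.96 | Hospital-level t, 13 df |
|---|---|---|---|---|
| 0 | near-equal | 5.0% | 6.0% | 4.9% |
| 0 | uneven | 5.0% | 6.0% | 4.8% |
| 0.5 | near-equal | 7.1% | 8.4% | 4.9% |
| 0.5 | uneven | 9.1% | 10.6% | 4.9% |
| 1 | near-equal | 9.8% | 11.3% | 5.2% |
| 1 | uneven | 13.5% | 15.4% | 4.9% |

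**4. Check with Poisson counts and a ward random effect.** This used 600 runs per cell, so each figure is good to about ±2 to 3 points. For s = 0, 0.5 and 1 it gave 6.0%, 7.8% and 11.3% with near-equal wards, and 4.7%, 9.3% and 14.0% with uneven wards. It agrees with step 3.

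None of these calculations models individual length of stay, which the planned model will take into account.

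**The case against.** **The randomised unit is not settled.** If wards were allocated one by one, as a literal reading of Study status suggests, ward-level clustering matches the design and most of the inflation disappears. This stands, and it is why the conclusion is conditional. It does not clear the protocol, because the two sections on setting and randomisation and the power calculation would then be wrong. Study status can also be read as shorthand for the ward counts that resulted from allocating hospitals.

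**The size depends on unstated quantities.** A reader might infer that the type I error is well above 5% as a matter of fact. The documents do not support that: the hospital share of the variance and the wards per hospital are not given, and with no variance between hospitals the error is 5-6%. A reader might also work with ICCs of 0.01 to 0.05 and reach about 17-23%. Those ICCs are not in the protocol.

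**The plan does account for clustering.** Ignoring clustering altogether would give 2 × [1 − Φ(1.96 / √2.32)], or about 20%. The ward effect absorbs part of the hospital variance, so that figure does not apply.

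**Part of the excess comes from the cut-off.** With no hospital variance, 1.96 alone gives 6.0% against 5.0% with t. The protocol does not fix the reference distribution for the primary model; the Z test it mentions belongs to the power calculation. The t columns above isolate the effect of the missing level.

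**Ward randomisation would not undo the reason for clustering.** The protocol clusters to limit contamination between individual staff members, which ward clusters may also serve to some degree. It stratifies by beds and nursing staff, not by hospital. So it does not follow that the contamination rationale would fall, or that hospital would become a blocking factor.

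**Conclusion.** The inconsistency is real. The protocol contradicts itself on the unit randomised, and its primary model leaves out the level that it names as randomised and powers on. If hospitals were randomised, any positive variance between them makes the specified test anti-conservative.

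At ICC 0.005 the type I error is roughly 10-14% with all of the ICC at hospital level, which is the protocol's own planning model; single settings ran from 9.1% (the approximation) to 15.4% (simulation). It is about 7-10% with half of the ICC there and 5-6% with none. These ranges rest on assumed layouts of wards over hospitals, on about 132 patients per ward, and on either a t or a 1.96 cut-off. The direction is certain under hospital randomisation; the size is not fixed by the document. Because the defect concerns the one primary test and stated text must change under either reading, it should be resolved before analysis.

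**What to change.** 1. State the unit of randomisation once, and make the Abstract, Setting and sample, Recruitment and randomisation, Power and sample size, Statistical analysis and Study status sections agree with it. Give the number of hospitals and of wards in each arm.
2. If hospitals were randomised, change the primary model to patients within wards within hospitals, with a hospital random effect, or analyse at hospital level. Base inference on the 15 hospitals: about 15 − 2 = 13 df, or permutation of hospital allocations within the randomisation strata. Apply the same structure to the secondary models, which are exploratory but whose intervals are also affected.
3. If wards were randomised individually, correct the two sections that name the hospital as the unit, and redo the power calculation with wards as clusters.

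The cost is some wording and one extra model term, with no new data. Confidence intervals will be wider. Small-sample inference also lowers the planned power: the same planning figures judged against t with 12 df (14 hospitals) give about 73% instead of 80%.

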#### *Qualitative analysis*

Qualitative data (SWOT analysis, possible barriers and facilitating factors for change, engagement in the new approach) will be analysed by thematic categorisation. A combination of deductive and inductive approaches will be used to gain an understanding of data. First, the taped interview data will be transcribed by researchers, which will be overseen by MV and MA to increase consistency, supervision and support the appraising process of the research group. The researchers will introduce themselves in the transcripts. Its content will be coded and further categorised by the specific themes by methods of Braun and Clarke's [97] phases of analysis process. Further, the validity and reliability of the coding will be checked by MA and TL by recoding and defining categories from a random sample of pages of the transcripts. For the qualitative data, the COREQ checklist by Tong et al. [98] will be used for reporting.

### **Dissemination**

The Department of Nursing Science at the University of Turku in Finland is nationally and internationally known for its research related to aggression in mental health care. It is also one of the leading research centres focusing on preferences of patients and nursing staff within the field in Finland. The Academy of Finland, as a main funder, together with Turku University Hospital, the University of Turku, in close collaboration with Hong Kong Polytechnic University of China (SAR), is providing the research infrastructure for the study as well as opportunities to spread knowledge from this project locally and internationally in collaboration with the WHO Western Pacific Region. The results of the study will be published in international referee-based, high-impact scientific journals, national vocational journals, newspapers, seminars, conferences and on the project's website and via social media campaign.

## SUPPLEMENT 1

### Discussion

This is a large-scale randomised controlled trial investigating whether staff educational intervention is associated with a decrease, no change or even increase in use of coercive methods and patient services, a changed global state, treatment satisfaction and quality of life, and team climate among staff members. This is a single-blind, two-arm stratified cluster trial, involving hospitals with psychiatric hospital beds across Finland. Based on good examples abroad and extending educational interventions supporting relatives' engagement in patients care, we believe that the study results may be beneficial in national and international contexts. Based on previous literature and our own experiences, we are prepared to face challenges in implementing and measuring the effects of the new intervention in mental health services and patient well-being [47, 53].

### Study status

To date, we have recruited 15 hospitals, in which a total of 28 psychiatric wards are willing to participate. Wards were randomised in May 2016 (13 intervention wards, 15 in comparison wards).

### List of abbreviations

DMC - Data Management Committee

CSQ-8 - Client Satisfaction Questionnaire

EU - European Union

GAS - Global Assessment Scale

ITT - Intent-to-treat

PASS - Power Analysis and Sample Size

Q-LES-Q-SF - Quality of Life Enjoyment and Satisfaction Questionnaire-Short Form

SWOT - Strengths, Weaknesses, Opportunities, Threats

TCI - Team Climate Inventory

WHO - World Health Organization

### Declarations

#### *Ethics approval and consent to participate*

The preparation phase of the trial (focus group interviews with staff members, and patients and relatives in associations) has been approved by the Ethics Committee of the University of Turku (33/2015). The proposal related to national register data has been assessed by the Ethics Committee of the University of Turku (code 41/2015). The trial has been approved by the Ethics Committee of the Hospital District of Southwest Finland (ETMK:9/1801/2016) and permissions to conduct the pilot study and realise the study in psychiatric hospitals have been granted by the study organisations in 2016. The study has been registered with ClinicalTrials.gov (NCT02724748 [99]).

Interviews with staff members, patient groups and relatives will be done on a voluntary basis and written informed consent will be obtained. The unit staff/research team members will approach patients and their relatives to explain the purpose of the study and its arrangements both directly and in written format. Patients and their relatives will be given the opportunity to ask questions about the study. Those assessed as lacking the capacity to give informed consent, and those who decline to participate, will not be interviewed. Staff and patient surveys are voluntary and will not include names, social security numbers, or any other identifiable information.

Participants will be informed that they have the possibility to withdraw their consent, and they will be made aware that data collected before withdrawal may be used for research purposes. Participants will also be informed that refusal or withdrawal from the study will not affect their position as staff members, health care clients or have effect on their relative's care.

### Consent for publication

Not applicable. Details, images, or videos relating to individual participants will not be published.

## SUPPLEMENT 1

### Availability of data and material

The data is usable for this study only.

### Competing interest

The authors declare that they have no competing interests.

